# The effect of postpartum vitamin A supplementation on breast milk immune regulators and infant immune functions: study protocol of a randomized, controlled trial

**DOI:** 10.1186/s13063-015-0654-9

**Published:** 2015-03-31

**Keywords:** Postpartum vitamin A supplementation, Infant immunity, Randomized controlled clinical trial

## Abstract

**Background:**

Because of limited impact on infant morbidity, mortality, and vitamin A status, the new guideline of the World Health Organization (WHO) does not recommend postpartum vitamin A supplementation (VAS) as a public health intervention in developing countries. However, breast milk contains numerous immune-protective components that are important for infant immune development, and several of these components are regulated by vitamin A.

**Methods/design:**

Postpartum women are being enrolled within 3 days (d) of delivery at a maternity clinic located in a slum area of Dhaka city and randomized to one of four postpartum VAS regimens (32/group, total 128). The regimens are as follows: Group 1: 200,000 IU VAS at <3 d and placebo at 6 weeks postpartum; Group 2: placebo at <3 d and 200,000 IU VAS at 6 weeks postpartum; Group 3: 200,000 IU VAS, both at <3 d and 6 weeks postpartum; Group 4: placebo, both at <3 d and 6 weeks postpartum. Breast milk samples at <3 d (before supplementation) and 4 months postpartum will be used to measure vitamin A and bioactive compounds. Infant blood samples at 2 and 4 months of age will be used to measure vitamin A, as well as innate and vaccine-specific immune responses. Dietary, anthropometric, and morbidity data are also being collected.

**Discussion:**

This is the first placebo-controlled randomized clinical trial of postnatal vitamin A supplementation to investigate the key bioactive compounds in breast milk, important for infant immunity, in relation to dose and time point of postpartum supplementation and whether such maternal supplementation improves infant immune status during the critical period of early infancy.

**Trial registration:**

ClinicalTrials.gov: NCT02043223, 5 December 2013

## Background

Vitamin A deficiency increases the risk of death from infections in children and is still a major public health problem in developing countries. At present, vitamin A supplementation (VAS) is recommended for children beginning at 6 months of age to reduce vitamin A deficiency and risk of death from infection. Up to age 6 months, breast milk is the only source of vitamin A for infants. However, there is ample evidence that, in addition to essential nutrients, breast milk contains numerous immune-protective components [1,2]. Proteomic analysis reveals 268 proteins in human milk, of which 44 are related to host defense, mostly involved in the immune system [3], and several of them are regulated by vitamin A [4-7]. However, studies on the effect of postpartum VAS on breast milk immune regulators are extremely limited. One study reported higher secretory IgA levels in breast milk after immediate postpartum VAS [8]. Another study demonstrated no effect on milk concentrations of immune factors including secretory IgA and IL-8 at 3 months after postpartum VAS within 1–3 weeks of delivery [9]. These studies lack follow-up data and data on other key immune regulators in breast milk or the effect of maternal VAS on infant immune development. Nevertheless, it is well characterized that the immunological composition of human milk changes over the lactation period [2,10]. To increase mothers’ vitamin A stores in developing countries, which are depleted during the course of pregnancy and lactation, and to increase the vitamin A content in breast milk, in 1997 the WHO/UNICEF/IVACG Task Force recommended 200,000 IU VAS of postpartum women within 6 weeks of delivery [11]. Because of limited impact on the infant vitamin A status, those guidelines were revised in 2001, and 400,000 IU VAS, divided into two equal doses, were recommended at least one day apart [12]. Systematic reviews found no impact of postpartum VAS on maternal and infant morbidity and mortality [13-15], and the new 2011 WHO guideline did not recommend postpartum VAS as a public health intervention [16].

However, in several studies mothers were supplemented with vitamin A within 6 weeks of delivery, without stratifying the supplementation time point during the postpartum period. This is a major limitation in studying the clinical impact of maternal supplementation, because colostrum (produced the first few days postpartum) is three times richer in vitamin A and 10 times richer in beta-carotene (provitamin A) than mature milk (produced 2 weeks after delivery). High-dose VAS failed to increase colostrum vitamin A levels in mothers with lower serum retinol levels [17]. Thus, vitamin A metabolism, immune-regulatory effect, and transfer to mammary gland differ if supplementation is carried out in the immediate or late postpartum period in regions where the deficiency is endemic. The primary objective of this study is to determine if postpartum VAS enhances immune components in breast milk and whether this effect is modified by the dosing regimen during the postpartum period (immediate or delayed). Secondary, exploratory objectives include the effect of postpartum VAS on infant immune status by determining microbial pattern recognition receptor-mediated innate immune responses, T cell responses, and vaccine-specific antibody-secreting plasma cell responses.

## Methods/design

### Study approval

The study protocol was peer reviewed and approved by the Research Review Committee (RRC) and Ethical Review Committee (ERC) of the International Centre for Diarrhoeal Disease Research, Bangladesh (icddr,b) (FWA-00001468; IRB-00001822).

### Study site and population

This study is being carried out at icddr,b, Dhaka, in collaboration with the Maternal and Child Health Training Institute (MCHTI) at Azimpur. Study participants live in the largest concentration of slums, located at the western fringe, having an urban slum population of about 1 million. MCHTI is the largest public maternity clinic located in that area. This clinic provides antenatal and prenatal care at minimal or no cost. According to the clinic registry, there are about 400 babies born per month. We are obtaining informed written consent from the pregnant women. During the immediate postpartum period, we also renew the consent of the mother and her willingness to have her infant participate.

### Study design

To test the impact on immune components of breast milk and infant immune function, we are carrying out a prospective, double-masked, randomized controlled clinical trial of postpartum vitamin A supplementation (VAS).

#### Inclusion/exclusion criteria

The inclusion criteria for postpartum women are as follows: (1) lives nearby MCHTI clinic, for convenience of follow-up visits; (2) ≥18 years of age; (3) free from diabetes, neoplasia, or other serious chronic or infectious diseases; (4) has given birth to a singleton baby; and (5) willingness to have the infant participate and adhere to the protocol. Inclusion criteria for newborn babies are: (1) free from congenital disease or a serious infection and (2) eligible for vaccination according to the MCHTI clinic policy.

#### Randomization and study intervention

After obtaining informed written consent, eligible postpartum women within 2 to 3 days of delivery are being block-randomized with a block size of 4 to achieve equal allocation ratios across groups. A computer-generated, randomized sequence within a block is utilized to assign women into the following four groups (n = 32/group, total 128) for the supplementation of 200,000 IU vitamin A and/or a placebo during immediate (<3 days, d) and/or delayed (6 weeks) postpartum periods (Figure 1).

**Figure 1 Fig1:**
[figure not shown]
**Study flow chart.**
^a^According to the national Expanded Program for Immunization (EPI) for newborn and infants. OPV, oral poliovirus vaccine; PENTA, pentavalent vaccines- a combination of five vaccines that comprise diphtheria, tetanus, whole cell pertussis, hepatitis B and haemophilus influenzae type b conjugate. ^b^Based on maternal supplementations **(Study interventions): Group 1:** 200,000 IU VA at <3 d and placebo at 6 wk; **Group 2:** placebo at <3 d and 200,000 IU VA at 6-wk; **Group 3:** 200,000 IU VA, both at <3 d and 6 wk; and **Group 4:** placebo, both at <3 d and 6 wk.

Group 1: 200,000 IU vitamin A at <3 d and placebo at 6 weeks postpartum;Group 2: placebo at <3 d and 200,000 IU vitamin A at 6 weeks postpartum;Group 3: 200,000 IU vitamin A, both at <3 d and 6 weeks postpartum; andGroup 4: placebo, both at <3 d and 6 weeks postpartum.

#### Safety considerations

We do not anticipate any serious adverse events as a result of once or twice supplementing with 200,000 IU vitamin A at 6 weeks apart in a community where the prevalence of low serum retinol (<1.05 μmoI/L) among lactating mothers is >26% with approximately 10% of them classified as deficient (serum retinol <0.70 μmol/L) and dietary sources of vitamin A are also limited (unpublished data). Earlier, similar doses of postpartum VAS were recommended by the WHO/UNICEF/IVACG Task Force [11,12]. Large doses of vitamin A are well tolerated by newly delivered mothers [18]. However, typical symptoms of acute hypervitaminosis A in adults include headache (presumably from increased intracranial pressure), nausea, vomiting, and occasionally fever and visual disorientation. These symptoms are generally transient and do not lead to permanent adverse effects [19]. It is also unlikely to have chronic vitamin A toxicity among study participants (symptoms are, for example, anorexia, dry itchy skin, osteoporosis, and hip fracture). These conditions can result from daily intakes of >25,000 IU vitamin A for >6 years or >100,000 IU vitamin A for >6 months [19-21]; nevertheless, there is wide inter-individual variability for the lowest intake required to elicit such toxicity. In addition, postpartum VAS shows no overall effect on disease transmission, for example, maternal-to-child transmission of HIV [22].

#### Sample size calculation

In this study, our primary aim is to compare the mean responses of immune markers in breast milk following postpartum VAS compared with a placebo. There are limited data available with human studies. In one study, supplementing postpartum women with a single 200,000 IU vitamin A dose increased secretory immunoglobulin A (sIgA) concentration in breast milk by 45.7% compared to a placebo within one day [8]. We are interested in determining if at least 20% higher immune markers (including sIgA) in breast milk persist at 4 months among women who receive a single dose of 200,000 IU vitamin A either at <3 d (Group 1) or at 6 weeks (Group 2) postpartum compared to the placebo (Group 4) and 10% higher responses among women who receive two doses of 200,000 IU vitamin A both at <3 d and 6 weeks (Group 3) postpartum compared to single-dosed postpartum women. In a one-way ANOVA design, sample sizes of 29 in each of the four groups achieves 80% power to detect our predicted differences using an *F*-test with 0.05 significance levels. The size of the variation in the means is represented by a standard deviation (SD) of 39.5 mg/dL of sIgA. The common SD within a group is assumed to be 126 mg/dL, a pooled value obtained from a previous trial [8]. There are no data available regarding immune measures of infants resulting from maternal VAS. In this project we consider that lymphocyte antibody responses in infants of the four maternal groups are the prime outcome variables which might link to the protection of infants from infection. With 29 infants per group, we will have >80% statistical power to detect a mean difference of 75% of the population standard deviation at α = 0.05 based on direct comparison between infants of the placebo group and infants of any of the three maternal VAS groups. Considering 10% attrition, our goal is to recruit 32 postpartum women into each of the four groups, for a total of 128 participants.

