### Data analysis plan

Statistical analyses will be done in SPSS 17.0 for Windows (SPSS Inc., Chicago, IL, USA). Data analysis will be conducted on intent-to-treat principles. Distributions of study variables will be analyzed to identify outliers and test assumptions of normality and equal variance. Data will be transformed to create normal distributions as needed. Randomization will be checked by evaluating infant sex, mode of delivery, gestational age, birth weight, mother age, BMI, and parity status using the *t*-test for continuous and the chi-square test for categorical variables. These variables will be used as covariates in multiple linear regression models to assess treatment effect on the continuous outcome variable of immune measures. If these adjustments have any considerable impact on the findings, the effect of the adjustment will be reported along with the effect without adjustment to evaluate whether the adjustment process interferes with the randomized comparisons. An interaction term, for example, treatment x postpartum time point of supplementation, will be used in mixed model multivariate analysis followed by inspection of univariate *F*-ratios. Interactions and main effects will be further analyzed for specific mean differences using *post hoc* analyses with a correction of alpha. Effect sizes associated with univariate *F*-statistics will be expressed as eta-squared (η^2^) for providing an indication of variance explained by the main effect or interaction. Effect sizes based on a specific difference in mean will be expressed as Cohen’s *d* for an indication of the magnitude of differences. Bivariate correlation in conjunction with multiple regression analysis will be used to evaluate inter-relationships among different immune measures associated with the effect of VAS.

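### The stated 80% power holds for the four-group F-test only; the single-dose and second-dose differences it is attached to have about 54–71% and 19–30%

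*Protocol article*

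**What the plan says.** The Sample size calculation sets out two differences for breast milk immune markers. The first is single dose against placebo: "We are interested in determining if at least 20% higher immune markers (including sIgA) in breast milk persist at 4 months" in Group 1 or Group 2 relative to Group 4. The second is two doses against one: "10% higher responses among women who receive two doses of 200,000 IU vitamin A both at <3 d and 6 weeks (Group 3") relative to single-dosed women.

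The power statement follows directly: "sample sizes of 29 in each of the four groups achieves 80% power to detect our predicted differences using an" F-test at the 0.05 level in a one-way ANOVA. Its inputs are "The size of the variation in the means is represented by a standard deviation (SD) of 39.5 mg/dL of sIgA" and "The common SD within a group is assumed to be 126 mg/dL, a pooled value obtained from a previous trial".

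No power is given for any pairwise milk-marker comparison. For the infant outcome, the same section does power a direct comparison with placebo (0.75 SD, more than 80%). The Data analysis plan leaves specific mean differences to post hoc "analyses with a correction of alpha", without naming the method or the number of comparisons.

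**The concern.** The differences the section predicts are contrasts between particular groups. The test it powers asks only whether the four means differ somewhere. A significant F-test can come entirely from two doses versus placebo and leave both named questions open: whether one dose helps, and whether a second dose adds anything. Power for the F-test is therefore not power for those contrasts.

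What is at stake is how a null result is read. The Discussion hopes to inform policymakers about postpartum supplementation. A non-significant single-dose or second-dose comparison, set against a stated 80%, could be taken as evidence of no effect when the chance of detecting the predicted difference was well below that.

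**Working it through.** **Inputs** (all from Sample size calculation): 29 evaluable women per group, four groups; alpha 0.05; SD of means 39.5 mg/dL; within-group SD 126 mg/dL; single dose = 1.20 × placebo; two doses 10% above single dose. Ten percent can be multiplicative (1.32 × placebo) or additive (1.30 × placebo); both are carried through.

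**1. Reproduce the stated figure.** f = 39.5/126 = 0.3135. Noncentrality λ = 116 × 0.3135² = 11.4. Noncentral F with 3 and 112 df at alpha 0.05 gives **80.4%**, as stated. Reading 39.5 as an SD with divisor 3 gives 67.0%, so 39.5 is the population SD (divisor 4) of the four means.

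**2. Recover the means.** The placebo mean m is not printed, so it is solved from the pattern.
- Multiplicative (1, 1.2, 1.2, 1.32): SD of pattern 0.1149, so m = 39.5/0.1149 = 344 mg/dL.
- Additive (1, 1.2, 1.2, 1.30): SD of pattern 0.1090, so m = 39.5/0.1090 = 362 mg/dL.

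The standardised differences below depend only on 39.5/126 and the pattern.

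**3. What drives the F-test.** In the multiplicative pattern the average is 1.18. The squared deviations are 0.0324 (placebo), 0.0004 for each single-dose group and 0.0196 (two doses), total 0.0528. Groups 4 and 3 supply 61% and 37% of this.

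**4. Power of each contrast.** For difference D with group weights c, δ = D / (126 × √(Σc²/29)), referred to noncentral t with 112 df, two-sided. The last column assumes 0.05/3 purely as an example, since the protocol names no correction.

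| Contrast | D, mg/dL (mult. / add.) | d (D/126) | Power at 0.05 | Power at 0.05/3 |
|---|---|---|---|---|
| One single-dose group vs placebo | 68.8 / 72.5 | 0.55 / 0.58 | 54% / 58% | 37% / 41% |
| Groups 1+2 pooled vs placebo | 68.8 / 72.5 | 0.55 / 0.58 | 66% / 71% | 49% / 54% |
| Group 3 vs one single-dose group | 41.3 / 36.2 | 0.33 / 0.29 | 24% / 19% | 12% / 9.5% |
| Group 3 vs Groups 1+2 pooled | 41.3 / 36.2 | 0.33 / 0.29 | 30% / 24% | 17% / 13% |
| Group 3 vs placebo | 110.0 / 108.7 | 0.87 / 0.86 | 91% / 90% | 81% / 80% |
| Groups 1+2+3 pooled vs placebo | 82.5 / 84.6 | 0.65 / 0.67 | 86% / 87% | 73% / 76% |

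Worked example, first row, multiplicative: the standard error is 126 × √(2/29) = 33.1, so δ = 68.8/33.1 = 2.08 and power is 54%.

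**5. Detectable difference.** An uncorrected pairwise comparison at n = 29 reaches 80% at about 93 mg/dL. That is 27% of 344 (26% of 362), against the 20% named.

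**6. Most favourable case.** With all 32 per group retained, both single-dose groups pooled and the additive reading, single dose vs placebo reaches 75% two-sided. Two doses vs pooled single dose reaches at most 32% (multiplicative reading).

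**7. Cross-check inside the section.** The infant calculation, 0.75 SD at 29 per group, recomputes to 80.1% by t-test. A pairwise test at this size therefore needs about 0.75 SD, whereas the named milk differences are about 0.55–0.58 and 0.29–0.33 SD.

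**The case against.** The strongest reply is that no figure is miscalculated. The section names a one-way ANOVA F-test, gives its inputs, and the result reproduces. On that view the predicted differences are simply the pattern of four means entered into the test, and the fault is loose wording. The first half stands: this is not an arithmetic error. The second half does not clear the text, because the sentence follows two specific contrasts and claims power to detect them.

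A reader might also infer that the trial is underpowered for its primary aim. The documents do not support that. The section's stated aim is supplementation compared with placebo, and under the same means all supplemented groups pooled against placebo would have 86–87% uncorrected, and Group 3 against Group 4 90–91%. The pooled contrast is not named as a planned test, so it does not rescue the sentence, but it rules out a general charge of low power.

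Three further limits stand:
- The reference to Group 1 or Group 2 can be read as one single-dose class, so 54% is the low end of a range that reaches 71%.
- The 0.05/3 figures assume a correction the protocol does not specify.
- Covariate adjustment and the mixed model might gain precision, by an amount the document does not allow one to estimate.

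Finally, the planned reporting of Cohen's d means that interpretation would not rest on significance alone, which softens the harm.

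**Conclusion.** The point holds as a misattribution. The 80% is correct for the omnibus test and incorrect for the differences it is said to cover. At two-sided 0.05 without correction, power is 54–58% for one single-dose group versus placebo, 66–71% with Groups 1 and 2 pooled, and 19–30% for two doses versus one. No two-sided reading examined brings either named contrast to 80%, and any alpha correction lowers the figures further. The second-dose question is weak on every reading.

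These powers are conditional on the 39.5 mg/dL having been built from the 20%/10% pattern, with the placebo mean back-solved. That is a reasonable inference, but the protocol does not state it. A higher placebo mean would raise the powers but break the match. At 500 mg/dL, for example, one single-dose group versus placebo would have 85%, but the multiplicative pattern would then give an SD of means of 0.1149 × 500 = 57 mg/dL, not 39.5. The 20% is also described as a minimum, and a larger true effect would have more power.

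**What to change.** Reword the power statement in Sample size calculation:

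- Say that 29 per group gives 80% power for the global four-group F-test only.
- State the assumed group means, including placebo, that produce the 39.5 mg/dL, and whether the 10% is multiplicative or additive.
- Report power, or the detectable difference, for single dose versus placebo and for two doses versus one, saying whether Groups 1 and 2 are pooled and using the alpha that will actually apply after correction. For an uncorrected pairwise comparison the detectable difference is about 93 mg/dL, roughly 27% of the implied placebo mean.
- Present two doses versus one as an estimate with a confidence interval, without a powered claim.
- If all supplemented groups versus placebo is the intended primary contrast, name it as such and give its power alongside.

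This is a change of wording. It needs no extra recruitment and no change of design. The only cost is a less favourable stated power for the named comparisons.

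### The >80% power for infant antibody responses holds only per comparison at an uncorrected 0.05; with alpha corrected for the three placebo comparisons it is about 65–68%

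*Protocol article*

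**What the plan says.** The Sample size calculation section of the protocol article sizes the trial on breast milk sIgA with a one-way ANOVA F-test, which gives 29 per group (32 after attrition). It then adds a separate claim for infant lymphocyte antibody responses, which it calls prime outcome variables: "With 29 infants per group, we will have >80% statistical power to detect a mean difference of 75% of the population standard deviation". The section ties this claim to a significance level of 0.05 and to pairwise tests of placebo against each supplemented group. It mentions no allowance for there being three such comparisons.

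The Data analysis plan describes a mixed-model multivariate analysis followed by univariate F-ratios. Interactions and main effects are then followed up for specific mean differences by post hoc "analyses with a correction of alpha". Neither the method nor the family is given. The same section also plans multiple linear regression of the immune measures on treatment and covariates, and says nothing about alpha there.

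The Background calls the infant objectives secondary and exploratory, and the Outcome variables section lists the infant responses as secondary.

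**The concern.** A difference between placebo and one supplemented group is a specific mean difference. The sample size section powers it at the full 0.05. The analysis plan says such differences are tested at a corrected alpha. Both statements are in the article, so the mismatch does not depend on a detail left to an unseen analysis plan.

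What is at stake is how a null infant result is read. A reader told that power exceeds 80% expects a true 0.75 SD difference to be missed at most one time in five. Under a single-step correction for three comparisons, it would be missed about one time in three.

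**Working it through.** **Inputs**
- Evaluable infants per group: n = 29 (Sample size calculation).
- Standardised difference: d = 0.75 (same section).
- Alpha: 0.05. Sidedness is not stated, so two-sided is assumed.
- Allocation: equal across the four groups (Randomization and study intervention).
- Correction: planned, method unnamed (Data analysis plan). The candidates below are assumptions.

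**Formula.** For two means with equal n, the noncentrality is d × √(n/2) = 0.75 × √14.5 = 2.856. Power is the probability that a noncentral t with this noncentrality exceeds the critical value. Degrees of freedom are 2 × 29 − 2 = 56 for a two-group test, or 4 × 29 − 4 = 112 with error pooled over four groups.

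**The plan's own figure**
- Uncorrected, df 56: critical value 2.003, power 80.1%.
- Uncorrected, df 112: critical value 1.981, power 80.8%.
- Normal approximation: 81.5%.
- One-sided 0.05, df 56: 88.0%.

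The >80% therefore reproduces. The difference detectable with 80% power is 0.749 SD at df 56, so 0.75 SD leaves no margin. At n = 28, power is 78.7%.

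**Corrected alpha, n = 29 per group, power per comparison at 0.75 SD**

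| Correction | Critical value | Power |
|---|---|---|
| Bonferroni, 0.05/3 = 0.0167, df 56 | 2.468 | 65.1% |
| Bonferroni, df 112 | 2.430 | 66.5% |
| Dunnett, three against control, df 112 | 2.382 (simulated) | 68.2% |
| Tukey, all six pairs, df 112 | 2.608 | 59.9% |
| Holm, only one group responds | stepwise (simulated) | about 67% |
| Holm, all three groups respond | stepwise (simulated) | about 74% |

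**Difference detectable with 80% power, three comparisons**
- Dunnett: 0.848 SD.
- Bonferroni: 0.861 SD (df 112) or 0.872 SD (df 56).

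**Sample size.** At 0.05/3, 80% power for 0.75 SD needs 39 evaluable infants per group by the t calculation. With no attrition (32 per group), Bonferroni power is 70.4% (df 56) to 71.6% (df 112).

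**If alpha is left uncorrected.** Three tests at 0.05 would have a family-wise error of 1 − 0.95³ = 14.3% if independent. They share the placebo group, so this is an approximate upper figure.

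**The case against.** **There is no arithmetic error.** The section states its alpha, sample size, difference and comparison, and on those inputs the figure is right. This stands: the fault is the mismatch with the analysis plan, and the calculation itself is sound.

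**The correction is unnamed.** A reader might take 65–68% as the trial's actual power. The document does not support that, because it fixes neither method nor family, and the choice of method can properly be left to an analysis plan. The range is conditional. The direction is not: every correction tried at n = 29 gives between 60% and 74% per comparison.

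**Other analyses keep their power.** The planned regression carries no stated correction, so a placebo-referenced coefficient tested there at 0.05 would match the power statement. The four-group F-test at 0.05 has 83.4% power if one supplemented group, or all three, differ from placebo by 0.75 SD. If all three differ by that amount, the chance that at least one corrected comparison is significant is about 87–89% (Bonferroni or Dunnett). All this is fair, and it rules out saying that the infant analysis as a whole is underpowered. But the article's claim concerns "based on direct comparison between infants of the placebo group and infants of any of the three maternal VAS groups", and the only step that names specific mean differences corrects alpha.

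**Splitting alpha further.** A reader might also divide alpha over the two antigens and two ages and arrive at still lower power. Nothing in the document says alpha is shared across them.

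**Pooling.** One contrast of all supplemented groups against placebo is a tempting remedy, but it gives up the dose and timing question that the Background sets as the trial's purpose.

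**Consequence.** The infant outcomes are secondary and exploratory, the article says no prior infant data exist, and it commits to reporting Cohen's d. This lowers the severity. It does not make the power statement agree with the analysis plan.

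**Conclusion.** The point holds in a limited form. The >80% is correct for a single placebo comparison at an uncorrected two-sided 0.05, and only just. It does not carry over to the alpha-corrected post hoc comparisons in the Data analysis plan. If the three placebo comparisons are the family, per-comparison power for 0.75 SD is about 65–68%, and the difference detectable with 80% power is about 0.85–0.87 SD. Across the methods tried, the range is 60–74%.

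This assumes two-sided tests, 29 evaluable infants per group and a correction covering at least the three placebo comparisons. Severity is minor to moderate: a stated power figure disagrees with the plan's own handling of alpha, for outcomes that are secondary and exploratory.

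**What to change.** Do one of the following.

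1. Name the correction and its family in the Data analysis plan, and restate the infant power at the corrected alpha. With three placebo comparisons, that is about 65–68% for 0.75 SD, or 80% for about 0.85–0.87 SD.
2. Keep the >80%, but say that it is per comparison and unadjusted. State that these secondary comparisons are exploratory and will be reported as group differences with confidence intervals, and make the Data analysis plan agree.

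Either is a change of wording. Neither alters the design, the recruitment target or the samples collected. The cost is a less favourable power figure under the first option, and a weaker claim for the infant comparisons under the second.
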